### Secondary analyses

To test ***Hypothesis 3***: Participants in the IYP will report significantly less pain, improved joint count, and mood compared to controls. The same methods used for the primary analyses will be used for the secondary analyses on pain intensity (averaged across the weekly NRS ratings taken during the initial 6-week IYP/control period) and mood. Consistent with ***Hypothesis 3***, we expect that the yoga group will evidence greater improvements on these measures over the 6-week treatment period relative to controls. We will also conduct similar within-group repeated measures analysis, as described in the primary analyses above, to examine changes in the secondary measures from baseline to post-treatment and follow-up. Consistent with ***Hypothesis 3***, we also expect that benefits will be maintained over the two-month follow-up period.

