**9. *Medication use ***will be assessed during the patients' weekly phone call/e-mail during which the ***Weekly Monitoring Form ***will be administered. These weekly forms will be used to gather ratings of patients' pain, fatigue, anxiety and depression using 0-10 scales; we will also assess the extent of physical activity during the past week and the extent (i.e., frequency/duration) of any home practice of yoga.

A ***weekly monitoring form ***will include specific questions about functioning, mood, pain, improvement, activity and medication use. The form is an important tool as patients' self-reported functioning will form the basis for understanding the action of yoga over time on symptoms. Thus, responses to the form will be used to determine the minimum and maximum number of yoga sessions needed to produce change. For participants who prefer completing this form online, an online link will be sent to them each week. Otherwise, the form will be telephone-administered by a trained research assistant once a week for two weeks preceding the intervention to ascertain baseline functioning, and then once a week during the intervention and control periods.

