### Primary analyses

To test ***Hypothesis 2***: Participants in the IYP will demonstrate significantly greater improvement in HRQOL and functioning compared to controls. The primary outcomes include the SF-36, PDI and the HAQ. Two sets of analyses will be conducted. The first set of analyses will compare the initial yoga and control groups immediately after the IYP and control phase, respectively. Separate mixed group (yoga vs. control) by time (baseline vs. post-treatment/post-control) repeated measure analysis of variance (ANOVA) will be conducted on the primary outcomes, or the non-parametric equivalent (Friedman procedure), in the event the assumptions for parametric analyses are not met. We will use the Tukey-Fisher criteria for post hoc mean/median comparisons under the ANOVA or Friedman model. Consistent with ***Hypothesis 2***, we expect a group by time interaction wherein the yoga group will report improved functioning from baseline to post-treatment compared to the control group. The second set of analyses will assess maintenance of treatment gains during the follow-up period. If yoga and control groups do not differ significantly on SF-36, PDI and HAQ scores at baseline, then data from the two groups will be combined in order to maximize power. If groups differ at baseline, each group will be analyzed separately. Changes in SF-36, PDI and HAQ scores across baseline, post-treatment and follow-up will be evaluated using separate within-group repeated measures ANOVAs; Friedman's procedure will be used if parametric assumptions are not met. Consistent with ***Hypothesis 2***, we expect significant improvements in functioning scores from baseline to post-treatment, persisting at follow-up.

We will also conduct an ***intent-to-treat (ITT) analysis***on primary outcomes to confirm our findings in completers by including all participants who enrolled in the study, using the last observation carry forward approach. Participants who drop out will be included in the analysis by utilizing outcome scores before attrition.

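### Pain is analysed as a six-week mean with no named baseline, while two planned pre-period weekly ratings are assigned to no pain test

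*Protocol article*

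**What the plan says.** Three parts of the protocol article bear on the pain test.

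- **Secondary analyses** names as endpoints "pain intensity (averaged across the weekly NRS ratings taken during the initial 6-week IYP/control period) and mood" and states that "The same methods used for the primary analyses will be used for the secondary analyses on pain intensity".
- **Primary analyses** describes that method as a mixed "group (yoga vs. control) by time (baseline vs. post-treatment/post-control) repeated measure analysis of variance (ANOVA"). Its time factor has two levels, one before and one after the six-week phase.
- **Exploratory variables**, item 9, has the weekly form collect "ratings of patients' pain, fatigue, anxiety and depression using 0-10 scales". When given by telephone, it is administered "once a week for two weeks preceding the intervention to ascertain baseline functioning, and then once a week during the intervention and control periods".

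Secondary outcomes separately defines pain as a single 0–10 rating of current pain. Preliminary analyses admits a baseline variable as a covariate only if the arms differ significantly on it.

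**The concern.** A mean over weeks 1 to 6 is one value per patient. The assigned test needs two, and Secondary analyses does not say what the first is. At least three choices are open: compare the means with no baseline, pair the mean with the single rating from the baseline assessment, or pair it with the two pre-period weekly ratings. They differ in precision, and the wording allows the choice to be made after the data are seen. The two weekly ratings are the most informative of the planned baselines, yet no section links them to this test. At stake is the precision of the randomised comparison for the pain part of Hypothesis 3.

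**Working it through.** **The plan's own figure.** The Sample Size section gives 27 per group for the treatment-by-time interaction (80% power, 0.05, medium effect) without the pre-post correlation, so it cannot be reproduced from the stated inputs alone. Change scores with d = 0.5 and r = 0.79 match it: 2 × (1.96 + 0.84)² × 2(1 − 0.79) / 0.5² = 15.7 × 0.42 / 0.25 ≈ 26.4, rounded up to 27. The effect size quoted there (0.46) is for the HAQ; none is given for pain.

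**Inputs.**
- From the document: 28 completers per arm (35 × 0.8); 6 ratings during the period and 2 before it; significance level 0.05, taken as two-sided.
- Assumed: equal correlation ρ between any two weekly ratings of a patient; each rating has SD 1; effect 0.5 SD of a single rating. The effect is either constant from week 1 (mean effect 0.5) or builds linearly to week 6 (mean effect 0.5 × (1+2+3+4+5+6)/36 = 0.292).

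**Formulas.** The variance of the six-rating mean is V6 = (1 + 5ρ)/6, that of the two-rating mean is V2 = (1 + ρ)/2, and their covariance is ρ. The variance that enters each test is:
- no baseline: V6
- group-by-time, two-rating baseline: V6 + V2 − 2ρ
- group-by-time, one-rating baseline: V6 + 1 − 2ρ
- ANCOVA, two-rating baseline: V6 − ρ²/V2

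Power comes from the noncentral t distribution with noncentrality (mean effect / √variance) × √(28/2).

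**Example, ρ = 0.5, constant effect.** V6 = 0.583 and V2 = 0.75.
- No baseline: 0.5/√0.583 × 3.742 = 2.45, power 67%.
- Group-by-time with two ratings: variance 0.583 + 0.75 − 1 = 0.333, noncentrality 3.24, power 89%.
- ANCOVA with two ratings: variance 0.583 − 0.25/0.75 = 0.25, noncentrality 3.74, power 96%.

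**Results** (linear build-up / constant effect):

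| ρ | No baseline | Group-by-time, one rating | Group-by-time, two ratings | ANCOVA, two ratings |
|---|---|---|---|---|
| 0.3 | 38% / 81% | 22% / 53% | 35% / 77% | 53% / 94% |
| 0.5 | 29% / 67% | 29% / 67% | 46% / 89% | 57% / 96% |
| 0.6 | 26% / 61% | 35% / 77% | 55% / 94% | 63% / 98% |
| 0.7 | 24% / 56% | 44% / 87% | 67% / 98% | 73% / 99% |

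Group-by-time beats ignoring baseline only if the baseline variance is below 2ρ. With two ratings this means (1 + ρ)/2 < 2ρ, so ρ > 1/3; with one rating it means ρ > 0.5. ANCOVA gains at any positive ρ.

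**Other scaling.** If 0.5 is counted in SDs of the six-week mean (normal approximation), power is 46% with no baseline. For ρ from 0.5 to 0.7 it is 70–95% for group-by-time with two ratings and 81–97% for ANCOVA. The ordering is the same.

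**The case against.** The strongest reply is that the pieces fit together on a natural reading. The two early ratings are collected expressly to establish baseline, Secondary analyses draws on the weekly ratings and speaks of improvement and of change from baseline, and a condensed article may leave the exact pairing to the full protocol or SAP. Much of this stands, and it rules out several stronger readings.

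- *That the test cannot be run.* A reader might infer this from the single six-week mean. Baseline pain is planned, both on the weekly form and at the baseline assessment. Once one value is named, the test is executable.
- *That the two ratings go unused.* They have a stated baseline purpose, and exploratory use of the weekly-form data is foreseen. What can be said is that no section assigns them to the pain test.
- *That unequal variances at the two time levels invalidate the ANOVA.* With two levels the interaction is a t-test on change scores. Pairing six ratings with one can cost efficiency but does not affect validity.
- *That a real benefit would probably be missed.* With a constant effect and ρ of 0.5 to 0.7, even the no-baseline test has 56–67% power. The 24–29% figures owe much to the assumed linear build-up, which lowers the average effect to 0.292 SD. The fix keeps the averaging and so does not remove that loss.

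Also, most of the power difference closes once the two ratings enter the plan's own test. ANCOVA then adds about 6 to 11 points under linear build-up and 1 to 7 under a constant effect.

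What remains is that the article fixes both the endpoint and the test without saying how they join, and that the conditional covariate rule in Preliminary analyses does not routinely bring baseline pain in.

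**Conclusion.** The point holds as a gap in the definition that can be closed at no cost. The loss is large if the analyst uses no baseline, and also with a single baseline rating in a group-by-time test when ρ is about 0.5 or less. It is modest if the two-rating baseline enters the named test and ρ is 0.5 to 0.7. These sizes rest on an assumed correlation, pain effect and time course, none of which the document gives. The preference for ANCOVA depends least on them, since it gains at every positive correlation, including 0.3 where group-by-time does not. Severity is minor: pain is one secondary outcome of a trial that calls itself preliminary and exploratory.

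**What to change.** In Secondary analyses, write: *Pain is the mean of the weekly NRS ratings in weeks 1–6 of the yoga/control period, compared between arms by ANCOVA with the mean of the two weekly NRS ratings taken before that 6-week period in both arms as covariate.*

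Two other places need to agree with it:
- **Exploratory variables**, item 9: state that the two early ratings precede the six-week comparison period in both arms. The present wording, "once a week for two weeks preceding the intervention to ascertain baseline functioning", could mean before the later yoga course for wait-list patients. Because the Randomization section allocates patients before the baseline assessments, also state whether these ratings are given before patients learn their arm.
- **Secondary outcomes**: reconcile the single current-pain rating with the six-week mean, and say which of the two serves the two-month follow-up.

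The cost is one sentence of analysis wording and two small alignments. The ratings are already planned, so there are no new data and no added patient burden.

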### Exploratory analyses for potential mediators and moderators

We will also examine potential mediators and moderators of treatment outcome. Regression analyses will be conducted to determine whether sociodemographic or clinical characteristics mediate or moderate treatment outcome. We will follow the procedures outlined in Cohen and Cohen [75] to calculate residualized change scores for the SF-36, PDI and the HAQ. Multiple regression analysis will then be conducted with outcomes separately; change scores (baseline minus post-treatment) will be regressed onto a set of predictor variables including group (yoga vs. control), the mechanism of interest (e.g., self-efficacy) and the interaction between the mediator/moderator and group. A significant interaction term indicates moderation [76] and post-hoc analyses will be conducted to examine the moderator variables. If evidence of mediation is found using the traditional Baron and Kenny approach, the Sobel test, a statistical test for mediation will be conducted to yield a more precise picture of mediation. Exploratory analyses will be conducted in the data derived from the weekly monitoring forms; for example, we will examine whether changes in overall physical activity may moderate treatment outcome.

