**Methods/Design:**

Seventy rheumatoid arthritis patients aged 16-35 years will be randomized into either the 6-week Iyengar yoga program (12 - 1.5 hour sessions twice weekly) or the 6-week wait-list control condition. A 20% attrition rate is anticipated. The wait-list group will receive the yoga program following completion of the first arm of the study. We will collect data quantitatively, using questionnaires and markers of disease activity, and qualitatively using semi-structured interviews. Assessments include standardized measures of general and arthritis-specific function, pain, mood, and health-related quality of life, as well as qualitative interviews, blood pressure/resting heart rate measurements, a medical exam and the assessment of pro-inflammatory cytokines. Data will be collected three times: before treatment, post-treatment, and two months following the treatment.

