### Design

A randomized control trial (RCT) design will be used to examine the impact of IYP for adolescents and young adults aged 16-35 years with RA on the primary outcomes of general and arthritis-specific functioning, and the secondary outcomes of DAS28, pain and mood.

The overall design of the study is depicted in Figure 2 below. After participants have completed the telephone screening and meet the study's eligibility criteria, they will be randomized into the IYP or usual care control group. All participants will be asked to fill out consent forms before their initial medical assessment, which includes a phlebotomy, measurement of blood pressure/resting heart rate, and a joint count conducted by a physician who will be kept unaware of group assignment. Before the medical assessment, a research assistant will send a link to the questionnaires for participants who choose to complete them online. A hard copy of the questionnaires will be taken to the medical assessment if the participant chooses to complete the paper-based version in a private medical office.

Those assigned to the IYP will then engage in the 6-week program; they will repeat the baseline assessments immediately following treatment and again at a two-month follow-up. Patients initially assigned to the wait-list group will continue their usual care. Both the yoga and control groups will either receive weekly phone calls or e-mails to monitor symptoms, medication use and physical activity. After 6 weeks, control participants will be re-assessed to ensure that they still meet study eligibility criteria; those that continue to meet criteria will then take part in the IYP. Following the IYP, participants will then repeat the baseline assessments at post-treatment and two-month follow-up.

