### Exploratory variables

**1. *Blood Pressure and Resting Heart Rate ***will be taken at each medical assessment to evaluate changes in autonomic nervous system activity using a non-invasive, portable, digital blood pressure monitor. A mean blood pressure/resting heart rate value will be derived by taking 2 readings, each 1 minute apart.

**2. *Cytokine Assays ***will be collected from subjects before and after the intervention, at the same time that the blood draws for ESR will be carried out. For the evaluation of pro-inflammatory cytokines, interleukin1-receptor antagonist (IL-1 RA), interleukin-6 (IL-6) and isolated PBMC will be incubated with LPS (500 μl) to yield a final concentration of 5 μg/ml (Ackerman et al., 1998). This dose of LPS has been found to yield optimal production of IL-1, and IL-6 following a 48-hour incubation. Concentrations of these pro-inflammatory cytokines from stimulated cell cultures will be determined by ELISA (R & D Systems). For IL-6, the ELISA intra-assay CV% is 3.1, inter-assay CV% is 2.5, sensitivity <0.7 pg/ml; for IL-1, the intra-assay CV% is 2.3, inter-assay CV% 4.1, sensitivity <1.0 pg/ml. For these assays, we will use high sensitivity kits. The subjects will be brought to a hospital laboratory where a trained phlebotomist will conduct the blood draws needed to assess disease activity in participants. For participants in the intervention group, these blood draws will be performed during a baseline assessment and again at the end of the yoga intervention. Wait-list controls will have their blood drawn at study entry, as well as before and after the yoga intervention.

**3. *Arthritis Self-efficacy Scale ***(ASES) [63] is designed to assess arthritis patients' beliefs that they can perform specific tasks or behaviors to cope with the consequences of chronic arthritis. The scale has 20 items to measure three subscales: pain, function and other symptoms. Reliability is good (α range = .76 - .89). The scale takes approximately 5 minutes to complete.

**4. *Coping Strategies Questionnaire ***(CSQ) [64] is a 42-item checklist measured on a 0-6 Likert scale designed to measure coping in relation to pain. Validity and reliability has been supported in a number of different pain populations, including arthritis patients [64-67]. A child version of the scale (CSQ-C) [34] has been validated and will be used for patients aged 16-20 years. The questionnaire takes approximately 10-15 minutes to complete.

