We recognize that the control group does not account for the group or social aspects of the IYP. However, we will assess the extent of the social support using qualitative methods to determine the extent to which these aspects may impact outcomes. The decision to include a wait-list control group was based on the consideration that including a group-based control intervention would be premature at this early stage of the clinical trial process. We plan to explore the initial feasibility, safety and efficacy of the IYP before moving on to a large-scale clinical trial employing a group-based control condition that controls for group effects related to the IYP. It is also possible that the results of the study will reveal null findings and no significant differences will emerge between the control and intervention groups. If this is the case, analyses will be conducted to determine possible causes of negative findings. Perhaps the intervention will only be effective for a sub-group (such as young adults) or for a limited number of outcomes. These findings will, in turn, inform future investigations of yoga for RA. Even if null findings occur, post-hoc analyses will prove valuable in refining further work in this area.

Despite these limitations, our study is an innovative contribution to the field of yoga research. One of the more novel aspects of the study is that we will use a mixed methodology assessment. This approach will allow us to learn more from the participants in ways that will help ensure the success of future studies and may lead to the formulation of additional hypotheses. A key feature of this project is the building of this study within a theoretical model that will guide us in testing specific pathways for IY effects, including the impact of psychospiritual aspects of IY on functional and HRQOL outcomes. These analyses represent the first step in the eventual delineation of salient moderators and mediators of the effects of yoga in this population. Based on the present findings, the model can be more fully explicated and tested in multi-center studies with larger samples.

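### The exploratory mediation test uses mechanisms measured only at the outcome visits, so it cannot show direction and can declare a pathway that does not exist

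*Protocol article*

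**What the plan says.** Under Exploratory analyses for potential mediators and moderators, "change scores (baseline minus post-treatment) will be regressed onto a set of predictor variables", the predictors being group, mechanism and their interaction ("including group (yoga vs. control), the mechanism of interest (e.g., self-efficacy) and the interaction between the mediator/moderator and group"). If the Baron-Kenny steps suggest mediation, a Sobel test follows. The section does not say whether the mechanism enters as a baseline, post-treatment or change value.

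On timing, the abstract says "Data will be collected three times: before treatment, post-treatment, and two months following the treatment". The Design section says of the yoga arm that "they will repeat the baseline assessments immediately following treatment and again at a two-month follow-up". The self-efficacy, coping, acceptance and mindfulness questionnaires are listed under Exploratory variables with no schedule of their own. Cytokine samples "will be collected from subjects before and after the intervention, at the same time that the blood draws for ESR will be carried out"; wait-list patients are also sampled at study entry.

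The weekly form runs in both arms between visits. It "will include specific questions about functioning, mood, pain, improvement, activity and medication use", and "These weekly forms will be used to gather ratings of patients' pain, fatigue, anxiety and depression using 0-10 scales". It also records home practice. Self-efficacy, coping, acceptance, mindfulness and cytokines are not on it.

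The Discussion describes "a theoretical model that will guide us in testing specific pathways for IY effects, including the impact of psychospiritual aspects of IY". The background section on psychosocial benefits expects gains in mindfulness and acceptance to lead on to better functioning, and the Rationale names IL-6 and IL-1 RA as a possible mechanism. The limitations discussed do not include same-visit measurement.

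**The concern.** A mediation claim needs the mechanism to move before the outcome, and it needs the mechanism-outcome association to be free of other explanations. Here both are read over the same interval. If yoga raises self-efficacy and that improves function, the data show group, mechanism and outcome all associated. If yoga improves function and that raises self-efficacy, the data show the same. Neither Baron-Kenny nor Sobel uses any information that could tell the two apart.

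A second route to a false result applies to the questionnaires. Mechanisms and all three primary outcomes are self-reported at the same assessment by patients who know their arm. A shared reporting tendency then creates the association the test looks for. This does not apply to the laboratory cytokines; for them the rivals are reverse causation and a common cause such as disease activity.

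At stake is which mechanisms later, larger trials are built to test.

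**Working it through.** **The plan's own figure.** There is none for this analysis. The sample-size section gives 27 per group for the group-by-time interaction; no power or error rate is stated for the mediation test, so there is nothing to reproduce.

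**Step 1: can any reading of the model order mechanism before outcome?**
- Baseline mechanism value: it precedes yoga and cannot carry yoga's effect. It can only moderate.
- Post-treatment or change value: concurrent with the outcome change.
- Post-treatment mechanism with two-month outcome: ordered in time, but not the planned model, and controls start yoga after six weeks, so no untreated comparison remains.

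The silence about which value enters therefore does not matter for a mediation reading.

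**Step 2: how often would the test declare mediation when there is none?**

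Inputs from the document: 28 completers per arm (56 in total), alpha 0.05 (taken as two-sided), pilot effect 0.46, and a medium effect (taken as 0.5). A larger effect comes from the plan's own sample size. The difference in change detectable with 80% power at 27 per group is about (1.96 + 0.84) × √(2/27) = 2.80 × 0.272 = 0.76 SD, or 0.78 SD with the t distribution.

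Assumed, because the document gives neither: the mechanism-outcome correlation r, and the yoga effect on the mechanism.

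Models, with T = group, d = effect in SD of change, and e, f, u independent standard normal:
- Reverse causation: Y = dT + e; M = rY + √(1−r²) f.
- Shared error: Y = dT + √r u + √(1−r) e; M = dT + √r u + √(1−r) f.

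Neither contains an effect of M on Y. Mediation is declared when the total effect, the a path (T to M) and the b path (M to Y given T) all have p < 0.05 and Sobel |z| > 1.96, where z = ab / √(a²·SE(b)² + b²·SE(a)²). The interaction term is left out for simplicity. There were 8,000 to 10,000 simulated trials per setting; ranges cover the two effect sizes and repeat runs.

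| Scenario | r | 0.46-0.5 SD | 0.78 SD |
|---|---|---|---|
| Reverse causation | 0.3 | about 1% | about 2% |
| | 0.5 | 6-8% | about 20% |
| | 0.7 | 16-20% | 48-49% |
| Shared error | 0.3 | 5-7% | about 27% |
| | 0.5 | 17-23% | 60-62% |
| | 0.7 | 27-32% | 73-74% |

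Where yoga affects neither measure, or does not move the mechanism at all, the rate is at most 1.6%. A larger sample does not help: with 70 analysed and 0.76 SD, shared error rises from 24% to 40% (r 0.3) and from about 60% to 75% (r 0.5).

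**Step 3: does the procedure detect direction?** With true mediation simulated (0.76 SD effect on the mechanism, r 0.7), the planned test passes in 47% of trials. With mechanism and outcome swapped it passes in 46%.

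**Step 4: would an earlier mechanism measurement help?** This illustration takes 0.76 SD, the full effect present by mid-treatment and, in the reverse-causation model, an outcome autocorrelation of 0.7.
- Reverse causation, r 0.7: same-visit test 46%; mid-treatment mechanism alone 33%; with mid-treatment outcome also adjusted 0.5%.
- Shared reporting specific to the occasion, r 0.5: 59% falls to 1%.
- Stable reporting style, r 0.5: 59% falls only to 32%.

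**The case against.** The analysis is labelled exploratory, and no aim or hypothesis concerns mediation. The background section on the biopsychosocial model says that not every pathway will be tested and leaves specific pathways to future larger trials. The Discussion calls these analyses a first step. The correlations behind the higher rates are assumed, and the largest effect is derived from the sample size rather than stated. The weekly form does collect mood and functioning in both arms, and mood is one of the postulated routes, so time-ordered data exist for that one.

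Much of this stands, and it rules out several stronger readings. A reader might infer that the test will usually find a false pathway. That is conditional: it needs yoga to move both measures and a moderate to strong correlation. A reader might infer that the efficacy results are compromised, but the primary and secondary comparisons do not use these models. A reader might take pathway testing to be the basis of the larger trial, but the Rationale bases that trial on feasibility, safety and efficacy. Shared self-report should not be extended to the cytokines.

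What the objection does not answer is direction. An exploratory label tells readers that a result is tentative; it does not tell them that the opposite causal order would have produced the same result. Nor is this a detail an analysis plan could settle, because it follows from when the measurements are taken.

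**Conclusion.** The concern holds in a limited form. As specified, the mediation test cannot distinguish a pathway from reverse causation or a common cause, nor, for the questionnaires, from shared self-report. That conclusion follows from the visit schedule and needs no assumption. How often a false pathway would be declared does rest on assumptions: the rate is negligible for reverse causation at r 0.3, and substantial when r is 0.5 or more and yoga moves both measures. The importance is moderate: the wording of the analysis and of the Discussion should change, because mechanism findings are meant to inform later trials.

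**What to change.** (a) In the mediator and moderator section and in the Discussion, state that same-visit mechanism-outcome results are associations. Fit the model in both directions (mechanism change between group and outcome, and outcome change between group and mechanism), report them side by side, and call neither mediation. The cost is a few regressions and some wording.

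(b) If a time-ordered test is wanted, add one 0-10 item each for self-efficacy, acceptance and mindful awareness to the existing weekly form in both arms. Use the week 2-3 value as the candidate mediator of the week-6 outcome, adjusted for the pre-intervention ratings, the baseline outcome and the functioning rating from the same week, which the form already collects. That last adjustment is essential: without it, an early functional gain can still raise the mechanism rating and persist to week 6. The weekly mood ratings can be used this way with no new item.

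The cost of (b) is a slight burden on patients and the lower reliability of single items. It does not reach cytokines, and it removes only part of a stable reporting style, so (a) applies in any case.

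### The exploratory mediation plan treats fixed traits as possible mediators, names two different change scores for one regression, and uses a needlessly conservative test (Baron-Kenny, then Sobel)

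*Protocol article*

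**What the plan says.** All three points are in the Protocol article, section Exploratory analyses for potential mediators and moderators.

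- **Candidate variables.** Regressions are to establish "whether sociodemographic or clinical characteristics mediate or moderate treatment outcome". A later sentence lists the regression terms as group, "the mechanism of interest (e.g., self-efficacy) and the interaction between the mediator/moderator and group".
- **Outcome.** The authors will "calculate residualized change scores for the SF-36, PDI and the HAQ". The next sentence says that "change scores (baseline minus post-treatment) will be regressed onto a set of predictor variables".
- **Test of mediation.** If the traditional Baron and Kenny approach gives evidence of mediation, "the Sobel test, a statistical test for mediation will be conducted", to give a more precise picture.

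The Discussion says of this work: "These analyses represent the first step in the eventual delineation of salient moderators and mediators". The Rationale adds IL-6 and IL-1 RA as a potential mechanism to be explored. Mechanism is not among the three specific aims or the three hypotheses. The section on the biopsychosocial model says that not every pathway will be tested in this preliminary study. No power or sample size is given for mediation.

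**The concern.** A mediator must be something that treatment can change. Age, sex and ethnicity are settled before randomisation, so yoga cannot act through them. They can only mark who benefits more or less.

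One regression needs one dependent variable. With two named, the choice can be made after the results on three outcomes are seen.

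The traditional Baron-Kenny steps start with a significant total effect. In a small trial that step can fail although the indirect path is real. Sobel then treats the product of two coefficients as normal, which loses more power.

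The stake is the next trial. The protocol says later trials will refine the conceptual model using this study's findings. An estimate with an interval serves that purpose better than a sequence of pass/fail tests.

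**Working it through.** **1. The sample.** Sample Size Determination and Power Analysis gives 35 per arm and 20% attrition: 35 × 0.80 = 28 per arm, 56 in total. This matches the completer figure stated under Exclusion criteria. The protocol has no mediation power figure to reproduce.

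**2. The two change scores.** Let β be the slope of post-treatment on baseline score, and Δ a between-arm difference in means.
- Raw change, with its sign turned to post minus baseline: contrast = Δpost − Δbase.
- Residualised change: contrast = Δpost − βΔbase.
- They differ by (1 − β)Δbase, which vanishes only if β = 1 or the arms start equal.

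With 28 per arm, the chance SE of Δbase is √(2/28) = 0.27 SD. The protocol does not give β. A one-SE imbalance moves the contrast by 0.5 × 0.27 = 0.13 SD at β = 0.5, and by 0.2 × 0.27 = 0.05 SD at β = 0.8. The pilot effect on the HAQ was 0.46. Raw change is also correlated with the baseline score whenever β differs from 1, which matters when baseline clinical variables are the predictors.

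**3. The mediation test.** The model is mediator M = a·group + error and outcome Y = c′·group + b·M + error, with error SDs 1, 28 per arm and two-sided 0.05. The paths a and b are assumptions. Baron-Kenny is read as a significant total effect, significant a, significant b and a shrunken direct effect.

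The total effect is ab + c′, and the SD of Y within an arm is √(1 + b²).
- *No direct effect (c′ = 0).* For (a, b) = (0.5, 0.39), (0.8, 0.39) and (0.8, 0.59), ab = 0.195, 0.312 and 0.472. In SD units: 0.195/1.073 = 0.18, 0.312/1.073 = 0.29, 0.472/1.161 = 0.41. The total-effect test then has only about 11%, 19% and 32% power, which caps the sequence.
- *Total effect at 80% power, as planned for the group-by-time effect.* This needs about (1.96 + 0.84) × √(2/28) = 0.75 SD, or 0.76 with the t distribution. The direct effects are 0.76 × 1.073 − 0.195 = 0.62, 0.76 × 1.073 − 0.312 = 0.50, and 0.76 × 1.161 − 0.472 = 0.41.

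Simulated detection of a true indirect effect (2,000 to 8,000 trials per scenario; ranges show differences between runs, which agreed within two or three points):

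| Shift a, slope b | Baron-Kenny then Sobel, c′ = 0 | Baron-Kenny then Sobel, total effect at 80% power | Baron-Kenny alone, total effect at 80% power | Sobel alone | Ungated interval for ab |
|---|---|---|---|---|---|
| 0.5, 0.39 | 2–4% | 17–18% | 32% | 19% | 35–38% |
| 0.8, 0.39 | 11% | 38–41% | 54% | 46–48% | 66–68% |
| 0.8, 0.59 | 28% | 63–65% | 70% | 74–75% | 83–84% |

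The last two columns do not depend on c′, because the estimates of a and b do not. The interval is a percentile bootstrap or a Monte Carlo interval; the two agree closely.

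**4. Other sample and path sizes.** Here the paths are per half-unit of group, so 0.39 means a shift of 0.78 SD, and the direct effect runs from 0 to 0.14 on the same scale.
- Paths 0.39/0.39, n = 56: sequence 10–26%, ungated 65%.
- The same paths at n = 70, if multiple imputation keeps everyone: 16–42% against 79%.
- Paths 0.59/0.59 (shift 1.18 SD), n = 56: 58–83% against 97%.
- Mediator shift 0.46 SD, slope 0.39, n = 56: 3–8% against about 31%.

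**5. False positives.** In three null scenarios the full sequence was positive at most 0.6% of the time. It can run a little higher when the slope and total effect are both larger. The bootstrap reached at most 5.5%.

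**The case against.** A reader might infer that the plan would miss most real mechanisms and report them as absent. The documents do not support that.

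- They give no path sizes. At large paths the sequence detects 58–83%.
- The lowest figures assume no direct effect, which is the worst case for the total-effect step. The Background expects several parallel routes (coping, mood, self-efficacy, acceptance, mindfulness, physical effects), so a direct effect beside any single mediator is likely.
- In the text, Baron-Kenny supplies the evidence and Sobel refines it. Nothing says that a Baron-Kenny positive is discarded if Sobel fails, so Baron-Kenny alone (32–70% when the total effect has 80% power) is a fair comparator too.

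A reader might also infer that all three faults cause lost power. They do not. The first two are errors of definition; the power loss comes from the gate, the Sobel approximation and the small sample.

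Nor is the repair free of error cost, because the present sequence has a very low false-positive rate.

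The wording can be read charitably. The regression sentence names self-efficacy, which yoga could change; clinical characteristics can change as well; and the parenthesis about baseline and post-treatment may only mark the interval. The section is headed exploratory and lies outside the aims.

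These points limit size and priority, and they stand. They do not remove the misassigned role of fixed traits or the double definition of the outcome. The ungated interval also detects more than the full sequence in every scenario with a true effect in the table.

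**Conclusion.** The point holds as three correctable faults in an exploratory analysis. The first two follow from the text alone.

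The size of the third rests on assumed paths, error SDs of 1, 56 completers, and reading the traditional Baron-Kenny steps as requiring a significant total effect. Without that step, power is close to Sobel alone. Against the full sequence, when the total effect has 80% power, the ungated interval gains about 17 to 30 percentage points (for example 35 − 18 = 17 and 68 − 38 = 30). Against Baron-Kenny alone the gain is about 3 to 14 points (35 − 32 = 3; 68 − 54 = 14). With no direct effect it is larger: 38 − 4 = 34 to 68 − 11 = 57.

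Small numbers limit every method, as the 31% for the ungated test at a shift of 0.46 SD shows. No primary or secondary conclusion changes.

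**What to change.** - **One outcome model.** Replace both change scores with the post-treatment score, adjusted for its baseline value. This is close to the residualised score already named.
- **Separate the roles.** Use sociodemographic and baseline clinical variables as moderators only. Limit mediators to measures yoga could change: self-efficacy, coping, acceptance, mindfulness, and the cytokines named in the Rationale.
- **Replace the gate and Sobel.** Report a percentile-bootstrap 95% confidence interval for the indirect effect, whatever the total-effect p-value, as exploratory estimation. A wide interval should not be read as absence of a mechanism.
- **Label multiplicity.** Four process measures and three outcomes give 4 × 3 = 12 intervals; adding two cytokines gives 6 × 3 = 18, before subscales are counted. At 5% each, up to 12 × 0.05 = 0.6 or 18 × 0.05 = 0.9 false positives would be expected if no indirect effect were real. State that the results are unadjusted.

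The cost is a few lines of text and code, with no new data. The trade-off is a per-test false-positive rate that rises from about 1% or less, in most null cases, to about the nominal 5%.
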